**Study goal**
Development of a machine learning algorithm based on relevant risk-factors and predictors to facilitate the diagnosis of depression
**Study design**
Prospective Study with three cohorts
**Inclusion criteria**
Sufficient ability to speak and understand German
Female and male subjects between 18–70 years
Ability to understand and sign the informed consent form
PHQ > 8, if depressed
**Exclusion criteria**
Cognitive limitations that interfere with reliable completion of questionnaires
Presence of a manic episode, bipolar disorder, schizophrenia spectrum disorder, active eating disorder, drug or alcohol dependence syndrome
Presence of uncontrolled systemic disease, uncontrolled somatic (other than metabolic or cardiovascular) /neurologic disease, current or recent (last month) trauma or infectious disease
Patients with acute suicidal ideation
Alpha-1-Antitrypsin deficiency
Pregnant or lactating women
**Discontinuation criteria**
Patients will be excluded if they develop an exclusion criterion during the course of the study. Data collected up to that point will be retained. The data collected up to that point will be retained in anonymized form, unless the participant requests deletion before ceasing their study participation

Table 1: This table provides an overview of the inclusion/exclusion criteria and the key data of the POKAL-PSY study.

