#### Secondary outcomes

Furthermore, we will implement a prospective algorithm predicting the severity of the participants' depressive symptomatology after one year. The results will be compared with the expertrating conducted at baseline. To ensure generalizability we will test the cross-sectional algorithm on the follow-up data. Further we will conduct a structural equation model (SEM) analysis at inclusion to better understand the underlying mechanisms that drive unipolar depression. Unsupervised cluster algorithms will be used to detect biomarker driven subtypes.

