### Power calculation

An a priori power analysis was performed to calculate the minimum of needed study participants to conduct a SEM analysis. We assumed a power (1-β) of 0.90 with an effect size of 0.15 and an alpha of 0.05. With these settings a sample size of at least 870 was required to achieve a robust model with 5 latent variables. With estimated screening failures of slightly less than 10% (e.g. development of bipolar disorder in the further course, or with inclusion concealment of a dependence illness) we aim to recruit 950 participants at inclusion. We aim to recruit a sample size of 475 patients with depression and 475 participants without depression. Recruitment in the project presented here will end when the sample size of 950 subjects is reached. Also, this is a sufficient number of participants for machine learning algorithms [106].

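### Table 1 carries the entry criteria into follow-up as withdrawal criteria, so some participants who do badly lose their later severity values and others are lost for transient reasons

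*Protocol article*

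**What the plan says.** The discontinuation rule in Table 1 reads: "Patients will be excluded if they develop an exclusion criterion during the course of the study". It exempts no criterion and provides for no return. On earlier data it says: "Data collected up to that point will be retained", in anonymised form and unless the participant asks for deletion.

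The exclusion criteria in the same table include:
- "Patients with acute suicidal ideation"
- "Presence of a manic episode, bipolar disorder, schizophrenia spectrum disorder, active eating disorder, drug or alcohol dependence syndrome"
- "current or recent (last month) trauma or infectious disease"
- pregnancy and lactation

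Follow-up is at four weeks and then yearly to five years (Study timeline). Under Secondary outcomes the authors write: "we will implement a prospective algorithm predicting the severity of the participants' depressive symptomatology after one year". Change in PHQ-9 and MADRS appears under Primary outcome, and the predictive value of baseline markers for change under Planned data analyses. The further course of disease is part of the second hypothesis, and the long-term prognosis of subgroups is an aim in the Abstract.

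The Power calculation allows for slightly less than 10% screening failures and gives as one example "development of bipolar disorder in the further course". Strengths and limitations mentions attrition bias only through moving away or reduced willingness.

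**The concern.** Criteria that are sensible for deciding who enters are reused to decide who stays. The study gives no treatment, so continued observation does not depend on continued eligibility for an intervention.

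The criteria fall into two groups that do different harm. Acute suicidal ideation and emergent dependence, and arguably emergent bipolar disorder, are tied to the course that the study wants to predict. Stopping assessment at these events removes later severity values in a way related to those values. Infection or trauma in the last month and pregnancy are transient and disturb mainly blood or impedance values. Ending participation for them loses numbers without need. Loss through infection is also related to the inflammatory predictors such as CRP.

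At stake are the one-year algorithm, the change analyses and the prognosis of the subgroups. An analysis plan written later can model the missing ratings but cannot recover them.

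**Working it through.** **1. The plan's own figures.** The Power calculation gives power 0.90, effect size 0.15, alpha 0.05 and five latent variables. The a-priori SEM lower-bound formula, with alpha two-sided (my assumption) and Šidák-adjusted for the 10 pairs of latent variables, uses:
- alpha' = 1 − 0.95^(1/10) = 0.0051, so z = 2.800; z for power = 1.282
- A = 1 − 0.15² = 0.9775; B = 0.15·arcsin(0.075) = 0.0113; C = 0.15·arcsin(0.15) = 0.0226; D = A/√(3 − A) = 0.6873
- H = (0.15/(2.800 + 1.282))² = 0.001351; t = A(π/6 − B + D) + H = 1.174
- n = [t + √(t² + 4AH(π/6 + √A + 2B − C − 2D))]/(2H) = 869.2, rounded up to 870

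The allowance is (950 − 870)/950 = 8.4%. Both figures reproduce and neither changes. They belong to a SEM on data at inclusion, so the 8.4% is not a yardstick for losses during follow-up.

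**2. Which analyses the rule reaches.**

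| Analysis | Data needed | Affected? |
|---|---|---|
| Algorithm for severity at inclusion, SEM, subtypes | Inclusion | Largely not; earlier data are kept |
| One-year severity, test of the algorithm on follow-up data | Up to one year | Yes |
| Change in PHQ-9 and MADRS | Follow-up | Yes |
| Long-term prognosis of subgroups | Up to five years | Yes |

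**3. Loss through transient criteria.** The protocol gives no rates. Assume a share q meets the infection or trauma criterion at each visit, independently across visits. There are two follow-up visits by one year and six by five years, so cumulative removal is 1 − (1 − q)² and 1 − (1 − q)⁶.

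| q (assumed) | By one year | By five years |
|---|---|---|
| 1% | 2.0% | 5.9% |
| 2% | 4.0% | 11.4% |
| 5% | 9.8% | 26.5% |
| 10% | 19.0% | 46.9% |

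These figures measure lost numbers, not outcome-related bias. The one-year column counts someone who meets the criterion at the one-year visit itself as removed. If that visit's ratings are kept, the loss of one-year ratings is smaller.

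**4. Bias through outcome-related criteria.** Take one-year severity as standard normal and remove exactly the worst share f. The mean of those left is −φ(z)/(1 − f), where z is the upper f quantile.
- f = 5%: −0.1031/0.95 = −0.109 SD
- f = 10%: −0.1755/0.90 = −0.195 SD

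The variance left is v = 1 − zφ(z)/(1 − f) − [φ(z)/(1 − f)]², which is 0.810 and 0.712. An assumed true R² of 0.25 becomes 0.25v/(0.25v + 0.75), that is 0.21 and 0.19.

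This hard cut is the extreme case for a given f. In a simulation of 1,000,000 draws, removal probability rose with severity instead (logistic, 1.5 per SD; assumed predictor correlation 0.3 or 0.5). The mean shift was about −0.03 SD at 2% removed, −0.06 at 5% and −0.12 at 10%. At 5% removed, the slope fell from 0.30 to 0.28 and from 0.50 to 0.47. Loss unrelated to severity shifted neither mean nor slope.

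**The case against.** The case for leaving the rule alone has real strength.

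- **The main analyses are cross-sectional.** Severity at inclusion, the SEM and the subtypes need only baseline data, which are kept. This stands: a reader might infer that the primary algorithm is biased, and the documents do not support that.
- **The Power calculation does not clearly contradict Table 1.** A reader might infer that people who later develop bipolar disorder are dropped from the SEM at inclusion. The text does not say so; it uses the term screening failure loosely in a recruitment allowance. What stands is that a later event is not a screening failure, and that the two places should be reconciled.
- **Infection is not an outcome.** Correct. The percentages in step 3 say nothing about outcome-related bias, and setting them against the 8.4% allowance would compare follow-up losses with a baseline requirement.
- **The bias figures are a worst case.** Severe depression and relapse are not exclusion criteria, half the cohort is planned to be non-depressed, and 90% are to come from GP offices. Nothing in the document supports 5% to 10% removed for outcome-related reasons. Ratings taken at the visit where an event is found may also be kept.
- **Stopping at a bipolar diagnosis is defensible** when the target is unipolar depression. This stands, provided it is defined as an event.
- **Analysis could mitigate the problem.** Competing-event, composite or weighting methods could use the retained earlier values. This helps only in part: severity after exclusion is not observed, and Table 2 lists the SCID only at inclusion, so later detection is not standardised.

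None of this supplies a reason to stop rating depression after acute suicidal ideation, dependence or a passing infection.

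**Conclusion.** The point holds for the follow-up analyses. As written, the rule ends data collection partly for reasons tied to the depressive course and partly for transient reasons, and the limitations section recognises neither.

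If those who do worse are removed more often, mean severity is understated and associations are attenuated. The size is unknown because the protocol gives no rates. For an assumed 5% to 10% removed in relation to severity, the shift is about 0.06 to 0.12 SD under graded removal and at most 0.11 to 0.20 SD under a hard cut. At an assumed 2% it is 0.03 to 0.05 SD. Avoidable loss through infection or trauma is about 2% to 19% by one year and 6% to 47% by five years, for an assumed 1% to 10% per visit.

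The documents do not support the stronger conclusions that the analyses at inclusion are invalid, that the target of 950 is wrong, or that the follow-up results are beyond repair.

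**What to change.** Amend the discontinuation rule, for data collection only and without touching clinical care:

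1. Apply the exclusion criteria to eligibility at inclusion.
2. Afterwards continue the scheduled assessments (PHQ-9, MADRS, IDS-SR, events) in every consenting participant, except where valid self-report is no longer possible.
3. For transient criteria, omit, flag or reschedule only the affected biomarker, HRV or impedance measurement.
4. Record emergent suicidal ideation, dependence and bipolar disorder as outcomes or defined intercurrent events, with a sensitivity analysis that censors at bipolar diagnosis.
5. State that retained baseline data enter the analyses at inclusion, and reword the Power calculation so that a bipolar diagnosis made later is not called a screening failure.
6. Name any remaining rule-based withdrawal among the sources of attrition.

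The cost is a short amendment and a few follow-up visits that would otherwise not take place. The sample size is unchanged. An early change is worth more than a late one: 230 participants were enrolled by September 2023, recruitment was expected to run to October 2027, and ratings missed in the meantime cannot be collected later.

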### Study timeline

We will perform a follow-up assessment 4 weeks after the participants’ inclusion into the study, and then annually for a total of 5 years, as indicated in Table 2.

**Table 2 Tab2:** Study assessment overview

	Study inclusion	After 4 weeks	Yearly follow up until 5 years
Observer rating	MADRS, GAF SIMPAQ, expert rating, SCID-CV	MADRS, GAF SIMPAQ	MADRS, GAF SIMPAQ, expert rating,
Self-rating questionnaires	Large questionnaire profile^1^	Small questionnaire profile^2^	Large questionnaire profile^1^
HRV measurements	At least 10 min (5 min supine/sitting each)	At least 10 min (5 min supine/sitting each)	At least 10 min (5 min supine/sitting each)
Bioimpedance scale	Tanita scale	Tanita scale	Tanita Scale
Laboratory assessments	Multiplex analysis, blood collection^3^	Multiplex analysis, blood collection^3^	Blood collection^3^
Vital parameters	Blood pressure, temperature, pulse	Blood pressure, temperature, pulse	Blood pressure, temperature, pulse

Large questionnaire profile^1^: socio-demographic data, family history, medical history, PHQ-9, PHQ-15, MCTQ, GAD-7, postal code, PID5BF + M, WHO-DAS, FEV, CTS, CTQ, PC-PTSD, PACIC, FEV, WHO-5, LSNS 6, BRS, UCLA LS 3, SSD-12, IDS-SR small questionnaire profile^2^: HTQ, PHQ-9, PHQ-15, MCTQ, GAD-7, WHO-DAS, FEV, SSD-12, IDS-SR Blood Collection^*3*^: fasting glucose, triglycerides, morning cortisol, CRP, AAT-1, IGF-1, cortisol, TSH, complete blood count, HbA1c, liver values

### Medical examinations

#### Clinical assessments

Depressive symptomatology is assessed using self-rated instruments (PHQ-9), the Inventory of Depressive Symptomatology (IDS-SR) [73] and observer ratings (MADRS) at inclusion and each follow-up [74]. At inclusion functionality will be rated using the General Assessment of Functioning (GAF) [75, 76]. To precisely detect possible exclusion criteria a SCID-5-CV rating is performed at study inclusion. All assessments are done by experienced and trained raters [77]. Furthermore, a rating is conducted where the raters need to describe their own impression concerning prognosis and give an estimate concerning the disease trajectory.

The abdominal circumference, as well as the hip circumference are measured standing with the upper body free with a measuring tape according to the guidelines of the WHO [78]. Blood pressure measurement (systolic, diastolic) and pulse is performed after 3–5 min of rest while sitting [79]. In addition, body temperature is determined with a tympanic thermometer in the morning [80].

Heart rate and HRV are measured using special chest straps (EcgMove4) from Movisens (Movisens GmbH), which determines body position. A HRV measurement is performed at each follow-up. The participants are kindly asked to be in an upright position for 5 min and lie for 5 min while breathing at a normal pace to achieve a resting state measurement [81]. If needed, participants can take breaks. Each participant should wear the belt at least for 10 min. Healthy controls will wear the belt for 24 h5 if possible. Blood is drawn between 8:00–10:00 in the mornings and analyzed at the Institute of Laboratory Medicine (LMU Hospital). Specifically, glucose, liver values, cholesterol (HDL and LDL), triglycerides, cortisol, TSH, AAT-1, IGF-1, CRP, and complete blood count are measured. The participants are asked not to smoke and to conduct an overnight fast before the examination. If participants are additionally willing to take part in the Munich Mental Health Biobank Project (MMBH), [82] further blood is drawn (9 ml Serum, 9 ml Li-Heparin, 7.5 ml EDTA, 2.4 ml RNA Extract) and stored at – 80 °C. Further analysis of MMHB blood samples is possible in following projects.

The participants are placed on a calibrated body analysis scale of the model TANITA MC-780MA-N (Tanita Corp., Tokyo, Japan) at the time of inclusion and at each subsequent follow-up. This scale uses state-of-the-art multi-frequency segmental bioelectrical impedance analysis (BIA) technology [83]. This technique is especially useful for providing an instant analysis of the participant’s health and fitness status and monitoring their progress over time [84]. Since food ingestion, regardless of macronutrient content, alters the BIA body composition estimates, patients are weighed after an overnight fast [85]. Furthermore, the participants are asked to take off their shoes as well as socks and wear light clothing. The body scale provides measurement parameters such as total body fat in kg and %, trunk fat mass in kg and %, total body muscle mass in kg and % (incl. arm and leg muscle assessment), total body water in kg and % (extra- and intracellular), visceral fat score, body mass index, basal metabolic rate in kcal and kJ, to record the subjects’ fitness and health [86]. To determine the BMI of the study subjects, their height is asked anamnestically.

#### Self-rating questionnaires

Table 2 shows which self-ratings are performed at each follow-up. To increase synergies patients are asked to fill out the Munich Mental Health Biobank Project (MMHBP) questionnaire battery as part of the POKAL-PSY study at inclusion [82].

Eating and sleeping habits will be assessed by the German version of the Three-factor-Eating-Questionnaire (FEV) [87] and the Munich Chronotype Questionnaire (MCTQ) questionnaire [88]. The simple physical activity questionnaire (SIMPAQ) will be taken to examine daily-life physical activities [89]. Also, participants will be asked about their drinking habits and whether they are smoking. Personality and anxiety traits, as well as somatic symptomatology will be measured using the Personality Inventory for DSM-5 Brief Form Plus (PID5BF + M) questionnaire [90], the Somatic Symptom Disorder-B Criteria Scale (SSD-12) [91], the Patient Health Questionnaire 15 (PHQ-15) [92], as well as the 7-item Generalized Anxiety Disorder Questionnaire (GAD-7) [93]. Personal history contains assessment of trauma with the childhood trauma questionnaire (CTQ) [94] and the Primary Care PTSD Screen for DSM-5 (PC-PTSD) [95], and family history, as well as medical history of psychiatric disorders will be gathered. The experienced loneliness is captured by the Lubben social network scale (LSNS 6) [96], as well as the UCLA 3-Item Loneliness Scale (UCLA LS-3) questionnaire [97]. Perceived Resilience and Wellbeing are measured by the WHO- 5 Well-Being Index [98] and the Brief resilience scale (BRS) [99]. Functional Outcomes are rated by performing the general assessment of functioning (GAF) [100] and participants are given the World Health Organization disability assessment schedule 2.0 (WHODAS 2.0) [101].

Table 2: Shows all planned examinations during the study period.

### Data and sample processing

The collected data in the POKAL-PSY study is captured in CentraXX (Kairos GmbH, Bochum, Germany), a laboratory information management system, which has already been used in other research projects at the department of psychiatry in Munich [102, 103]. CentraXX allows the collection and management of all relevant data of study participants [71]. The pseudonymization of the data is guaranteed by the CentraXX application [104].

### Outcome assessment

#### Primary outcome

Our primary outcome is the development of an algorithm that predicts the severity of unipolar depression with biological markers. We will use the routine blood laboratory markers, as well as the HRV data and only include single items concerning the self-rating questionnaire, if necessary. We hypothesize that IGF-1 and AAT-1 will be biological markers that facilitate diagnosing unipolar depression and hence will mainly drive the prediction together with the HRV data. We will use the PHQ-9 and the MADRS at baseline and follow-up to measure changes in depressive symptomatology as well as their severity [48]. Supervised algorithms like decision trees and support vector machines will be used to determine which factors drive the severity of depression at inclusion.

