## Introduction

Unipolar depression is a common disorder worldwide, with a 12-month prevalence of 4.6% [1]. Unfortunately, only 41% of the affected patients who wanted treatment for their disorder (71%) receive treatment that meets minimum standards [1]. At the same time, depression is one of the most debilitating diseases and imposes a significant challenge to both individuals and society. According to WHO, depression causes 6% of the burden of disease in Europe, if measured in disability-adjusted life years (DALYs) [2, 3]. The worldwide point-prevalence of a depressive disorder was 9.8% (95% CI: 6.7–14.1%) within the years 1994–2003 and has risen to 15.4% (CI: 12.9–18.3%) between the years 2004 and 2014 [4, 5].

Moreover, a patient's psychiatric history was found to be correlated with higher age at graduation on the one hand and unemployment on the other [6]. Early onset of depression was associated with dropout from secondary education [7]. In the context of employment, 5.1% of all days absent from work are attributed to depressive disorders and thus, along with chronic pain disorders, have the greatest negative effect on job attendance [8]. The prognosis is worse the more time passes until diagnosis and adequate therapy is established [9]. Currently, only 55% of depressed patients seeking treatment in primary care settings are detected. Especially, if there are other somatic comorbidities present, mental health disorders are underdiagnosed [10, 11]. While also most psychiatric care is delivered in primary care settings [12], delayed diagnosis and inadequate treatment leads to an increased socioeconomic burden and outcome [13].

Primary care physicians could screen for unipolar depression with the Patient Health Questionnaire 9 (PHQ-9) [14], as it is also recommended by the U.S. preventive task force [15]. Since the PHQ-9 is a self-rating questionnaire, heterogeneous response behavior can’t be avoided, and more extensive diagnostics are needed to determine whether someone has depression [16]. Although diagnostic accuracy is typically higher for clinically experienced psychiatrists, a thorough clinical interview still requires time and experience. Currently, there are no established biological markers that could facilitate and accelerate the diagnostic process for primary care physicians.

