### Planned data analyses

Categorical data will be one-hot-encoded if suitable and summarized with percentages and confidence intervals. For ordinal data the median will be given as well as the interquartile range and for continuous data we calculate the mean as well as the standard deviation and the confidence intervals. Demographic and baseline characteristics in the study arms will be compared with suitable statistical tests. Since multiple comparisons will be performed significant *p*.values will be reported false discovery rate corrected [107]. With the cross-sectional data at inclusion a SEM analysis will be conducted [108]. Furthermore, we will investigate the predictive value of baseline biological parameters for change in depressive symptomatology. In addition, we will design a classification algorithm using all relevant data detecting which participant is depressed. This approach involves the implementation of multiple supervised machine learning algorithms to thoroughly assess their performance. We will evaluate each algorithm during the analysis stage and subsequently select the one that yields the most favorable results. These algorithms may include, but are not limited to, support vector machines, decision trees, and neural networks. Each of these algorithms will be carefully applied and evaluated in the context of our research question. Furthermore, we will use multimodal stacked algorithms to assess the generalizability of different clinical questionnaires and biomarkers separately. To ensure the robustness of our algorithm selection and model performance assessment, we will employ a leave-site-out nested cross-validation approach in each model. This mitigates the risk of overfitting and ensures generalizability. Since the eventual goal of our algorithm is the implementation in a clinical context and to guide general practitioners, we plan to develop a sequential prediction model, which reduces the number of required data modalities and diagnostic uncertainty, as described by Koutsouleris et al. [109]. Sequential stacking models can be used to reduce the data required to produce optimum prediction scores. This method can greatly increase clinical applicability since physicians will be only asked for additional information if needed to achieve satisfactory predictive accuracy [109].

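### The primary biomarker algorithm may draw on self-rating items from the instruments that define its target, and the depression classifier has no stated reference standard although a SCID-5-CV is done at inclusion

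*Protocol article*

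**What the plan says.** Primary outcome, on the aim: "Our primary outcome is the development of an algorithm that predicts the severity of unipolar depression with biological markers". On measurement: "We will use the PHQ-9 and the MADRS at baseline and follow-up to measure changes in depressive symptomatology as well as their severity". No order of priority is set between the two instruments. On predictors, the section names routine blood markers and HRV, and adds that the analysts will "only include single items concerning the self-rating questionnaire, if necessary". It does not say when an item becomes necessary or which questionnaires may supply one. Table 2 lists the PHQ-9 and IDS-SR in both self-rating profiles.

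On who counts as depressed, the only depression-specific entry in Table 1 is "PHQ > 8, if depressed". Planned data analyses adds a second algorithm: "we will design a classification algorithm using all relevant data detecting which participant is depressed". It names no reference standard.

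Clinical assessments gives the structured interview one purpose: "To precisely detect possible exclusion criteria a SCID-5-CV rating is performed at study inclusion". The Introduction says of the PHQ-9 that it is a self-rating and that "more extensive diagnostics are needed to determine whether someone has depression".

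**The concern.** A predictor that is a component of the outcome correlates with it by construction. If PHQ-9 items may enter a model whose target is the PHQ-9 total, or a label cut from that total, accuracy partly measures the questionnaire against itself. The article hypothesises that IGF-1, AAT-1 and HRV will carry the prediction. A high headline accuracy from an item-assisted model would say little about that.

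The contingent wording makes this more likely to matter. Items come in when the markers fall short, which is when they would hide the shortfall. The classifier has a related gap: without a named reference standard, the screening cut-off is the obvious default label, although the article itself regards the PHQ-9 as insufficient to determine depression.

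**Working it through.** **Step 1. Roles that the article gives each instrument.**

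| Instrument | Entry | Severity target | Possible predictor | Other stated use |
|---|---|---|---|---|
| PHQ-9 | Cut-off above 8 (Table 1 says PHQ; reading this as PHQ-9 is an inference) | Yes | Not excluded (self-rating) | none |
| MADRS | No | Yes | Not excluded from the classifier | none |
| IDS-SR | No | Not named as target | Not excluded (self-rating) | Assesses depressive symptoms |
| SCID-5-CV | Exclusions | No | Not stated | none |

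The PHQ-9 can hold three roles at once. The SCID-5-CV, scheduled at inclusion without restriction to a cohort, has no stated role in the classifier.

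**Step 2. Size of the overlap when the PHQ-9 is the target.** The article gives no figure on this point; its 870 and 950 belong to the structural equation model and are not involved. It also gives no inter-item correlation, so r is an assumption. For nine items of equal variance and common correlation r, with S the sum of k items and T the total:

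- Cov(S, T) = k(1 + 8r)
- Var(S) = k(1 + (k − 1)r)
- Var(T) = 9(1 + 8r)
- R² = Cov² / (Var(S) × Var(T)) = k(1 + 8r) / [9(1 + (k − 1)r)]

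| r | Cronbach alpha = 9r/(1 + 8r) | One item | Two items |
|---|---|---|---|
| 0 | 0 | 1/9 = 0.111 | 2/9 = 0.222 |
| 0.3 | 0.79 | 3.4/9 = 0.378 | 6.8/11.7 = 0.581 |
| 0.5 | 0.90 | 5/9 = 0.556 | 10/13.5 = 0.741 |

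Even with unrelated items (r = 0), one item explains 11% of its own total. For scale, a marker correlated 0.15 with the target explains 0.15² = 2.3%. The 0.15 is borrowed from the article's power calculation and is an assumption here.

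**Step 3. The same with 0-3 items and a label of total above 8.** This is a simulation of 400,000 persons with assumed item thresholds, which put about 36% above 8 (the plan recruits 475 of 950, or 50%, as depressed). Here r is the correlation on the latent scale.

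| r | Two items: R² | Two items: AUC | Two items + three pure-noise markers: R² | Three markers, each 0.15 with severity: R² | Same: AUC |
|---|---|---|---|---|---|
| 0.3 | 0.526 | 0.844 | 0.526 | 0.045 | 0.601 |
| 0.4 | 0.610 | 0.874 | 0.610 | 0.049 | 0.606 |
| 0.5 | 0.681 | 0.900 | 0.681 | 0.052 | 0.609 |

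A model with two PHQ-9 items and markers that carry no information performs as well as the items alone.

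**Step 4. When the MADRS is the target.** PHQ-9 items are not part of the MADRS, so the formula in Step 2 does not apply. What remains is shared symptom content. In the same simulation, one PHQ-9 item explains 0.327 to 0.485 of the PHQ-9 total, but 0.15 to 0.25 of an external rating assumed to correlate 0.8 with latent severity. The problem is smaller but present.

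**Step 5. Cross-validation.** Leave-site-out nested cross-validation guards against overfitting. It does not remove this overlap, because the same items build the same total at every site.

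**The case against.** The strongest reply is that much of this rests on what the article leaves unsaid. Four stronger readings are tempting, and the text does not support them.

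- **That the plan uses PHQ-9 items as predictors.** It does not say so. No instrument is named, and Table 2 lists many self-ratings unrelated to depressive symptoms, such as sleep, eating and loneliness. PHQ-9 items are permitted, not prescribed.
- **That PHQ above 8 is the classifier's label.** This is an inference. The criterion can be read as a threshold for people already judged depressed; eligibility is also checked with the treating practitioners, and the primary-care comparison cohort is described as free of psychiatric disorders. What can be said is that no reference standard is stated.
- **That the primary claim cannot fail.** It can. The hypothesis that IGF-1, AAT-1 and HRV mainly drive the prediction is refuted if symptom items dominate, and the stacked models assess questionnaires and biomarkers separately. These are real safeguards, but neither is made the criterion for the primary outcome.
- **That label error dilutes the primary result.** If a fraction q of each group is mislabelled, mean differences shrink by the factor 1 − 2q (0.8 at 10%, 0.6 at 20%). That concerns only the classifier, not a severity score, and the documents give no error rate.

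It is also fair that lists of excluded features usually belong in an analysis plan, which is not shown. That would answer a mere omission. Here the article itself states a contingent rule for adding self-rating items to the primary model and sets two targets without priority. Followed as written, that rule allows the overlap.

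**Conclusion.** The concern holds in this form: the article lets items of a target-defining instrument enter the primary algorithm under an undefined condition, sets no priority between two severity measures, and names no reference standard for the classifier while giving the SCID-5-CV only an exclusion purpose. Good accuracy could therefore be reported with little biomarker contribution.

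The size depends on assumed inter-item correlations. Over 0.3 to 0.5, one or two PHQ-9 items would outweigh markers of the strength assumed above. The percentages apply only if PHQ-9 items are used and the PHQ-9 is the target. The documents do not show that this will happen, only that nothing stated prevents it. The point should be settled before analysis, because it decides what the primary outcome can demonstrate.

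**What to change.** 1. Make the performance of the blood-marker plus HRV model the primary result, with blood pressure, medication, age and gender handled as confounders as the section on mediating variables already plans. Report any questionnaire-augmented model separately, as an increment over that model.
2. Name one primary severity measure in advance and report the other as secondary. The observer-rated MADRS is a natural choice: it is already collected and does not share items with the entry screen.
3. Bar items and totals of the PHQ-9, IDS-SR and MADRS as predictors of the depression score or label.
4. Use the SCID-5-CV diagnosis at inclusion as the reference standard for the baseline depressed/not depressed classifier, with the PHQ above 8 label as a sensitivity analysis.

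All the data are already scheduled and recruitment is expected to run to October 2027, so the change is one of wording. The costs are that reported accuracy will probably be lower and that an unknown number of participants will change label. Table 2 also schedules the SCID only at inclusion, so tests of the algorithm on follow-up data must use the severity score.
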